### Intervention description {11a}

The intervention exists of a recurrence-focused follow-up approach with routine imaging and serial serum tumor marker testing. The follow-up scheme of the RADAR-PANC trial is based on current surveillance guidelines after resection for PDAC as recommended by the National Comprehensive Cancer Network (NCCN) [11]. This intense follow-up scheme was chosen to increase the chance of early diagnosis of disease recurrence. For the first 2 years after surgery, clinical evaluation, serum carbohydrate antigen 19–9 (CA 19–9) testing, and contrast-enhanced CT imaging of chest and abdomen is performed every 3 months.

Follow-up of patients and related procedures (i.e., blood draws, CT scans) in this study can be performed at the participating hospital, referring hospital, or central coordinating hospital. Study-related follow-up is performed at 3, 6, 9, 12, 15, 18, 21, and 24 months after surgery. For the first follow-up evaluation, patients need to be randomized within the first 3 to 4 months post-surgery. Follow-up appointments are made by the trial coordinator in consultation with the treating clinician. If possible, outpatient clinic visits are combined with CT scan appointments; blood samples are obtained simultaneously.

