#### Recurrence diagnosis

If disease recurrence (local and/or distant) is suspected on the basis of a follow-up CT scan, with or without elevated tumor markers, pathological confirmation is strongly advised. If the results remain inconclusive or pathology cannot be obtained, additional imaging (magnetic resonance imaging (MRI) and/or positron emission tomography CT (PET-CT)) may be considered. Consensus on the presence of a recurrence should be obtained in a multidisciplinary meeting (e.g., based on imaging, elevated CA 19–9, and clinical evaluation).

If disease recurrence is diagnosed, best supportive care (BSC) or systemic and/or local therapy is offered at the discretion of the treating clinician in both trial arms, which is the current standard practice, and trial-related follow-up will end. It is encouraged to offer treatment to all patients in whom there are no contraindications based on clinical condition (performance status), comorbidity, or specific exclusion criteria for systemic and/or local therapy. Patients can be offered to participate in intervention trials on management of pancreatic cancer recurrence. In the Netherlands, within the DPCG, two intervention studies for the treatment of PDAC recurrence have been simultaneously initiated: the ARCADE trial (NCT04881487), investigating the efficacy of stereotactic body radiation therapy on survival after recurrence and quality of life in patients with isolated local PDAC recurrence, and the TIMEPAN trial (NCT04897854) studying the optimal timing of start of systemic treatment for asymptomatic metastasized PDAC.

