### Outcomes {12}

The primary outcome is overall survival, defined as the time from the date of PDAC resection until the date of either death from any cause or last follow-up.

Secondary outcomes are the following:Patient-reported quality of life and worry of cancer recurrence, as measured by PROMs questionnaires within the PACAP-PROMs and PACOPS project: general EORTC QLQ-C30 and EQ5D-5L, pancreas-specific EORTC QLQ-PAN26, HADS, and WOPS.Compliance to recurrence-focused surveillance, measured as the percentage of patients that either accepts or refuses participation in the intervention-arm, i.e., is willing to undergo recurrence-focused follow-up.Disease-free survival, defined as the interval between the date of PDAC resection and the date of first radiological signs of recurrence, or last follow-up if recurrence is not observed. Preferably, recurrence is proven by a biopsy showing pathological confirmation of recurrent PDAC. However, recurrence can be clinically confirmed with growth of a suspicious lesion on consecutive CT scans and elevation of CA 19–9 (> 37 U/ml) and/or activity on PET-CT following consensus in a multidisciplinary meeting.Clinical and radiological patterns of disease recurrence:◦ Asymptomatic recurrence is defined as PDAC recurrence detected by CT imaging during follow-up, in the absence of suspected symptoms. If PDAC recurrence is discovered due to a significant patient-initiated complaint that is new or has been increased in severity or frequency, disease recurrence is defined as symptomatic.◦ Localization of recurrence is categorized using five categories: (1) isolated locoregional recurrence: recurrence in the pancreatic remnant, locoregional lymph nodes, or surgical bed, such as soft tissue along the celiac or superior mesenteric artery, aorta, or around the pancreatojejunostomy site; (2) isolated distant recurrence: recurrence restricted to a single organ or site; (3) local + distant recurrence: simultaneous occurrence of both isolated locoregional recurrence and isolated distant recurrence; (4) multiple recurrence: recurrence at multiple distant sites; and (5) peritoneal carcinomatosis.The yield of CT surveillance and role of serum tumor marker testing in detecting PDAC recurrence, by calculating diagnostic accuracy values, i.e., sensitivity, specificity, positive predictive values, and negative predictive values.Eligibility for additional (experimental) treatment at time of recurrence diagnosis, based on the Eastern Cooperative Oncology Group (ECOG) or Karnofsky performance state, or inclusion criteria for study-related treatment of recurrence.Reasons to refrain from treatment for recurrence (i.e., non-eligibility, deteriorated condition, patient’s wish, doctors’ advice, progression during treatment, etc.).Patients’ tolerance to treatment for recurrence, measured by the reasons to stop treatment for recurrence (i.e., per protocol, deteriorated condition, patient’s wish, doctors’ advice, progression during treatment etc.).Morbidity associated with recurrence-focused treatment.Overall costs of recurrence-focused surveillance vs. costs as incurred with current non-standardized follow-up. Cost-effectiveness is examined through the EQ5D questionnaire and calculated using a Markov model.

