### Statistical methods

#### Statistical methods for primary and secondary outcomes {20a}

The latest version of R Studio will be used for statistical analysis.

Baseline characteristics will be reported using standard descriptive statistics. Success of randomization will be evaluated by eye-balling whether the distribution of baseline characteristics between the intervention and control group is even. Primary analysis will be performed according to the intention-to-treat principle. As such, patients randomized to the intervention arm of the trial who refuse recurrence-focused surveillance following the TwiCs design will be analyzed as part of the intervention group. The main study parameter is overall survival, measured as the time from the date of PDAC resection to the date of death. Patients are censored at the time of last known follow-up visit documented if no event occurred. Overall survival rates will be reported as median with 95% CI and will be calculated by the Kaplan–Meier survival curve method. Log-rank test will be used to compare survival between the intervention and control group. One- and 2-year survival probabilities will be calculated. Univariate Cox-proportional hazard analysis will be used to assess the crude effect of a recurrence-focused surveillance strategy on survival. In addition, adjusted effect estimates will be calculated using a multivariable Cox-proportional hazard model, including potential confounders for symptomatic PDAC recurrence. To address potential confounders for which the multivariable analysis needs to be adjusted, a Directed Acyclic Graph was designed on https://www.dagitty.net (Fig. 3). It is hypothesized that a recurrence-focused postoperative surveillance strategy leads to the detection of PDAC recurrence in an asymptomatic stage, which increases the probability to undergo treatment for recurrence, possibly improving survival. The association between postoperative surveillance strategy and overall survival is therefore fully mediated through presence of symptoms at the time of recurrence diagnosis and subsequent administration of recurrence treatment. Given that the median overall survival after resection of PDAC is 21 months and 1- and 2-year survival rates are 75% and < 50%, respectively, we expect that during our follow-up period at least 50% of included patients (*n* = 153) will experience an event. The number of variables included in the multivariable analysis is based on the rule of thumb of ~ 10 events per variable, where a categorical variable counts for the number of categories. Consequently, multivariable analysis is adjusted for 15 baseline covariates that are considered to be the most important, i.e., age (continuous), sex (male/female), and predictors that reflect an (un)favorable tumor biology or treatment course, including performance status (continuous), preoperative CA 19–9 value (continuous), tumor location (head/distal), resection margin status (R0/R1), tumor size (continuous), number of positive lymph nodes (continuous) and tumor differentiation (poor/well-moderate), and administration of adjuvant therapy (yes/no). Given that recurrence treatment is considered a mediator, and not a confounder, no adjustment for recurrence treatment is required. Because administration of neoadjuvant therapy is known to affect preoperative CA 19–9 values, resection margin status, tumor size, and number of positive lymph nodes, neoadjuvant treatment will not be adjusted for. Postoperative complications are deemed to affect the receipt of adjuvant therapy and will thus not be included in multivariable analysis. Results will be presented as hazard ratio’s (HR) with corresponding 95% confidence intervals (CI). A two-tailed *P-*value < 0.05 will be considered statistically significant.

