Sponsor: The sponsor is the party that commissions the organization or performance of the research, for example a pharmaceutical company, academic hospital, scientific organization or investigator. A party that provides funding for a study but does not commission it is not regarded as the sponsor, but referred to as a subsidizing party
Symptomatic recurrence: Recurrent PDAC discovered due to a significant patient-initiated complaint that is new or have been increased in severity or frequency
TwiCs: Trials within Cohorts
WMO: Medical Research Involving Human Subjects Act (in Dutch: Wet Medisch-wetenschappelijk Onderzoek met Mensen
WOPS: Worry of progression of cancer scale

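### Symptomatic and asymptomatic recurrence are defined on different criteria, so patients with symptoms whose recurrence is found on a scheduled CT fit neither class, almost all of them in the intervention arm

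*Protocol article*

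**What the plan says.** Under the recurrence-pattern outcome, Outcomes {12} gives two definitions. The first is: "Asymptomatic recurrence is defined as PDAC recurrence detected by CT imaging during follow-up, in the absence of suspected symptoms". The second applies the symptomatic label in this case: "If PDAC recurrence is discovered due to a significant patient-initiated complaint that is new or has been increased in severity or frequency". The Abbreviations list repeats both, the second as "Recurrent PDAC discovered due to a significant patient-initiated complaint that is new or have been increased in severity or frequency". Neither place says how to class a recurrence that meets neither definition.

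In the intervention arm, Intervention description {11a} provides that "contrast-enhanced CT imaging of chest and abdomen is performed every 3 months" for two years, with clinical evaluation at the same visits. The Abstract (Methods) says that controls are generally imaged only when symptoms appear. Sample size {14} expects about 5% of controls to have routine imaging.

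The analysis section {20a} treats the effect of surveillance on survival as "fully mediated through presence of symptoms at the time of recurrence diagnosis" and the recurrence treatment that follows. Symptom status also appears in the objective on prognostic factors for asymptomatic recurrence (Objectives {7}) and in the additional analyses {20b}.

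**The concern.** A usable pair of classes should cover every recurrence and divide them on one criterion. Here one class is defined by the patient's state and the other by the event that led to the scan. Surveillance changes the trigger by design, so the classification depends on the arm as well as on the patient.

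Take two patients with the same new back pain. The control reports it, is scanned because of it, and is symptomatic. In the intervention patient it comes to light at a scheduled visit, and the CT due that day shows recurrence. Symptoms are present, so the case is not asymptomatic. The scan would have been done anyway, so the complaint did not lead to the discovery and the case is not symptomatic.

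At stake are the secondary outcome on recurrence patterns, the prognostic-factor objective, and the mediation analyses. The causal model needs symptom status at diagnosis. A variable that partly records the detection route would differ between arms even if symptoms did not, and that difference could be taken as support for the proposed mechanism.

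**Working it through.** **Do the definitions cover every case?** Cross symptoms at diagnosis with the route of detection:

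- No symptoms, found on CT: asymptomatic.
- Symptoms, and the patient's complaint led to the discovery: symptomatic.
- Symptoms, but found on a scheduled CT that they did not prompt: neither class.
- No symptoms, and not detected by CT: neither class. This group is narrow. Abbreviations accepts two of three criteria for clinical confirmation, so raised CA 19-9 plus PET-CT activity can suffice. In the surveillance scheme, however, CA 19-9 is drawn alongside CT, and Recurrence diagnosis presents PET-CT as an additional step after a suspicious CT.

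**How large could the third group be?** The protocol gives no asymptomatic rate to reproduce, so this is an illustration.

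From Sample size {14}: 153 patients per arm, 80% acceptance, 5% routine imaging in controls.

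Assumed: 70 to 80% of patients recur; 20% of accepters' recurrences come to light through a complaint between scans; a share s = 10 to 30% of scheduled-CT recurrences have symptoms that were not the trigger. A complaint that does lead to a scan counts as the trigger, whoever raised it first.

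- Accepters: 153 × 0.80 = 122.4.
- Recurrences R: 122.4 × 0.70 = 85.7 to 122.4 × 0.80 = 97.9.
- Found on scheduled CT: 0.80 × R = 68.5 to 78.3.
- Unclassified: 0.80 × R × s = 68.5 × 0.10 = 6.9 to 78.3 × 0.30 = 23.5, or about 7 to 24 patients.
- Controls on the same assumptions: 153 × 0.05 = 7.65 routinely imaged. Then 7.65 × 0.70 × 0.80 × 0.10 = 0.4 to 7.65 × 0.80 × 0.80 × 0.30 = 1.5 patients.

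Shares of accepters' recurrences (R cancels):

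| s | Unclassified, 0.8s | Recorded symptomatic | Symptoms present, 0.2 + 0.8s | Asymptomatic, all in denominator, 0.8(1 − s) | Asymptomatic, unclassified dropped, 0.8(1 − s)/(1 − 0.8s) | Asymptomatic, unclassified defaulted to it |
|---|---|---|---|---|---|---|
| 10% | 8% | 20% | 28% | 72% | 78% | 80% |
| 20% | 16% | 20% | 36% | 64% | 76% | 80% |
| 30% | 24% | 20% | 44% | 56% | 74% | 80% |

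Applied literally over all recurrences, the wording gives a correct asymptomatic share but understates the symptomatic share by 8, 16 or 24 points. Dropping the unclassified raises the asymptomatic share by about 6, 12 or 18 points. Defaulting them to asymptomatic raises it by 8, 16 or 24. Calling them symptomatic removes both errors, but the written definition does not allow it.

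**The case against.** The strongest reply is that the asymptomatic definition already guards against inflation. A patient with elicited symptoms fails the condition "PDAC recurrence detected by CT imaging during follow-up, in the absence of suspected symptoms", so counting that patient as asymptomatic would break the text. This stands. A reader might infer that the asymptomatic rate is inflated as a matter of course, but the document states neither a default nor an exclusion. The literal wording still misstates the symptomatic class.

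A reader might also infer that treatment eligibility is inflated in the intervention arm. Outcomes {12} accepts performance status "or inclusion criteria for study-related treatment of recurrence", and one companion trial is described as "studying the optimal timing of start of systemic treatment for asymptomatic metastasized PDAC". But the two routes are alternatives, so a fit symptomatic control qualifies on ECOG or Karnofsky status. The companion trial's inclusion criteria are not in the document, and the Discussion describes it more broadly, as for disseminated disease. One route to eligibility may depend on symptom status, and both named trials are presented as Dutch while this trial also recruits in the UK. That does not show an arm difference.

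It is also fair that the consequences are limited. Recurrence patterns are reported descriptively, and symptom status is not a covariate in the survival model. The full protocol or the case report form might hold a rule for residual cases, and multidisciplinary meetings act as an endpoint panel. But the article does define both classes, twice and in the same mismatched terms, so this is a fault in what is stated and not detail left out. Without blinding, and with local clinicians responsible for data collection, residual cases may be settled by people who know the allocation.

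**Conclusion.** The two definitions use different criteria and are not exhaustive. The main gap lies almost entirely in the intervention arm, and the trigger-based class does not measure the mediator named in {20a}. Symptomatic recurrence is therefore understated in that arm. Inflation of the asymptomatic share is a risk that depends on how unclassified patients are handled.

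The size rests on assumptions from outside the protocol, chiefly s = 10 to 30%. The figures show how the error scales with s and are not estimates of it. The effect on the mediation results cannot be sized from the document. The primary analysis of overall survival does not use symptom status and is unaffected. The point concerns secondary and mechanistic results and should be settled before they are analysed.

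**What to change.** Classify every recurrence in both arms by one rule: symptomatic if new or worsened symptoms were documented at the time of recurrence diagnosis, whatever the detection route, and asymptomatic otherwise. Take this from visit or referral notes. Record the trigger (scheduled scan, CA 19-9 or complaint) as a separate variable. Use symptom status, not the trigger, in the mediation analysis. Optionally, report eligibility by performance status separately from eligibility for the recurrence trials.

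The cost is one or two extra case report form fields and some incomplete retrospective documentation. A fixed symptom list completed before each scan result would be cleaner but is not practical: controls and their clinicians are not notified of allocation, and 219 of 306 patients were already enrolled by January 2, 2024. The reported asymptomatic proportion in the intervention arm may be lower than under a more permissive classification.

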
Data on the incidence of PDAC recurrence, compliance to a recurrence-focused surveillance strategy, clinical, and radiological patterns of recurrence, eligibility for treatment of recurrence, administration of recurrence treatment, as well as type of treatment, reasons to refrain from recurrence treatment, and patient tolerance to recurrence treatment (i.e., completion of treatment as planned) will be analyzed and reported using descriptive statistics. Chi-square or Fisher’s exact test are used to compare categorical variables as appropriate. Parametric continuous variables are presented as mean ± standard deviation (SD) and are compared using the Student’s *t*-test. Non-parametric continuous variables are presented as median with interquartile range (IQR) and are compared using the Mann–Whitney *U* test. Patient-reported outcomes at each time point during follow-up will be compared to baseline scores using a generalized linear mixed model approach to assess a difference in patients’ quality of life and worry of cancer recurrence between the trial arms. Scores will be presented as mean (± SD), changes from baseline as mean differences (MD) and estimates will be calculated to represent a difference in MD between groups with corresponding 95% confidence intervals (CI). Minimally important differences (MIDs) for the EORTC QLQ-C30 will be interpreted based on Musoro et al. for available quality of life domains [34]. If not specified, a ≥ 10-point change is considered meaningful. Disease-free survival and post-recurrence survival will be assessed using Kaplan–Meier survival curves and reported as median with 95% CI. The log-rank test will be used to compare groups. Cox proportional hazards model will be used when appropriate. Stratified analyses will be performed regarding pattern of disease recurrence and type of additional treatment. Various baseline parameters (e.g., sex, age, body mass index (BMI), Charlson Comorbidity Index (CCI), ECOG score, postoperative complications, (neo)adjuvant therapy, resectability status, preoperative CA 19–9 values, tumor location, resection margin status, vascular resection, tumor (T) stage, lymph node (N) stage, tumor differentiation, perineural growth) will be collected. The yield of CT surveillance and role of serum tumor marker testing is assessed by calculating diagnostic accuracy values, i.e., sensitivity, specificity, false-positive and false-negative values. Cost-effectiveness is calculated using a Markov model.

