## Abbreviations

ASCO: American Society of Clinical Oncology
Asymptomatic PDAC recurrence: PDAC recurrence detected by CT imaging during follow-up, in the absence of suspected symptoms
BMI: Body mass index
BSC: Best supportive care
CA 19-9: Carbohydrate antigen 19–9
CCI: Charlson comorbidity index
CI: Confidence interval
Clinically confirmed recurrence: 2/3 Of the following criteria: -Growth of a suspicious lesion on consecutive CT scans, -Elevation of CA 19–9 (> 37 U/ml), -Abnormal activity on PET-CT
CT: Computed tomography
CTCAE: Common Terminology Criteria for Adverse Events
CWS: Cancer worry scale
Disease-free survival: The interval between the date of surgery and either the date of first radiological signs of recurrence, or last follow-up if recurrence is not observed
DPCG: Dutch Pancreatic Cancer Group
DSMB: Data Safety Monitoring Board
EORTC QLQ-C30: Cancer-specific health-related quality of life
EQ-5D-5L: Non-disease specific health-related quality of life
ECOG: Eastern Cooperative Oncology Group
ESMO: European Society for Medical Oncology
FOLFIRINOX: Fluorouracil, leucovorin, irinotecan, and oxaliplatin
HADS: Hospital anxiety and depression scale
HQRL: Health-related quality of life
HR: Hazard ratio
IAP/EPC: International Association of Pancreatology/European Pancreatic Club
IQR: Interquartile range
MD: Mean differences
MID: Minimally important difference
MREC/METC: Medical research ethics committee (MREC); in Dutch: medisch ethische toetsing commissie (METC)
MRI: Magnetic resonance imaging
NCCN: National Comprehensive Cancer Network
NFU: The Netherlands Federation of University Medical Centers; in Dutch: Nederlandse Federatie van Universitaire Medische Centra
NVvH: In Dutch: De Nederlandse Vereniging voor Heelkunde
Overall survival: The time from the date of resection of PDAC until either the date of death from any cause or date of last follow-up
PACAP: Dutch Pancreatic Cancer Project
PACOPS: Pancreas Cancer: Observations of Practice and Survival
PDAC: Pancreatic ductal adenocarcinoma
PDAC recurrence: Pathologically or clinically proven recurrence of PDAC
PET-CT: Positron emission tomography—computed tomography
PROMs: Patient reported outcome measurements
QoL: Quality of life
Radical resection: Macroscopically radical resection, i.e., R0-R1 resection
RAKU/RACU: Regional Academic Cancer center Utrecht
RH: Relative hazard
UK: United Kingdom
SBRT: Stereotactic Body Radiation Therapy
SD: Standard deviation

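### CA 19-9 sensitivity is biased upward through recurrences confirmed without biopsy, because CA 19-9 above 37 U/ml is itself one of the confirming criteria

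*Protocol article*

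**What the plan says.** **Outcomes {12}** makes diagnostic accuracy a secondary outcome: "The yield of CT surveillance and role of serum tumor marker testing in detecting PDAC recurrence, by calculating diagnostic accuracy values", listing sensitivity, specificity and both predictive values. **Statistical methods {20a}** repeats the analysis with a slightly different list: "role of serum tumor marker testing is assessed by calculating diagnostic accuracy values, i.e., sensitivity, specificity, false-positive and false-negative values". The role of tumour markers in detecting recurrence is also a secondary objective under **Objectives {7}**.

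The target condition is defined in **Abbreviations**: "PDAC recurrence: Pathologically or clinically proven recurrence of PDAC". The clinical route appears in three places:

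- Outcomes {12}, within the definition of disease-free survival: "growth of a suspicious lesion on consecutive CT scans and elevation of CA 19–9 (> 37 U/ml) and/or activity on PET-CT", following multidisciplinary consensus.
- Abbreviations: "Clinically confirmed recurrence: 2/3 Of the following criteria: -Growth of a suspicious lesion on consecutive CT scans, -Elevation of CA 19–9 (> 37 U/ml", with abnormal PET-CT activity as the third criterion.
- Recurrence diagnosis: consensus may be, for example, "based on imaging, elevated CA 19–9, and clinical evaluation".

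Biopsy is preferred and strongly advised but not required. MRI or PET-CT may be considered when results are inconclusive or pathology cannot be obtained. Nothing in the article limits the accuracy analysis to biopsy-proven cases or names a reference standard free of CA 19-9.

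**The concern.** The index test is part of the reference standard. Among true recurrences without a biopsy, one with raised CA 19-9 needs only CT growth to be confirmed. One with normal CA 19-9 needs CT growth and PET-CT activity. Marker-negative recurrences therefore have a harder path into the denominator of sensitivity, and those that fail to enter are false negatives that are never counted.

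Three-monthly CA 19-9 is a core part of the intervention, and the dissemination plan foresees results entering treatment guidelines. An inflated sensitivity would make a normal marker look more reassuring than it is.

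**Working it through.** The article states no expected sensitivity, specificity or precision for CA 19-9, so there is no planned figure to reproduce. The check has two parts: which cases the rule admits, and how large the effect could be under stated assumptions.

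**1. Which unbiopsied cases the rule admits, taken literally**

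The Outcomes {12} rule is read here as CT growth plus at least one of raised CA 19-9 and PET-CT activity.

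| CT growth | CA 19-9 > 37 U/ml | PET-CT activity | Outcomes {12} | Abbreviations (2 of 3) |
|---|---|---|---|---|
| yes | yes | no or not done | recurrence | recurrence |
| yes | no | yes | recurrence | recurrence |
| yes | no | no or not done | not confirmed | not confirmed |
| no | yes | yes | not confirmed | recurrence |

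The third row shows the bias: marker-negative lesions drop out. The fourth row shows that the two definitions disagree on whether CT growth is required.

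**2. Simple illustration for sensitivity**

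Inputs, all assumed: true sensitivity s; share of recurrences biopsied b; share of the unbiopsied that are PET-positive p. All recurrences are taken to show CT growth, biopsy and PET-CT are independent of CA 19-9, the accuracy analysis uses the same 37 U/ml cut-off, and the rule is applied strictly.

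Marker-positive recurrences are all confirmed. Marker-negative ones are confirmed with probability v = b + (1 − b)p. Hence

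apparent sensitivity = s / [s + (1 − s)v].

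- b = 0.3, p = 0.1: v = 0.3 + 0.7 × 0.1 = 0.37. For s = 0.70: 0.70 / (0.70 + 0.30 × 0.37) = 0.70 / 0.811 = 0.863.
- b = 0.7, p = 0.3: v = 0.7 + 0.3 × 0.3 = 0.79. For s = 0.70: 0.70 / (0.70 + 0.30 × 0.79) = 0.70 / 0.937 = 0.747.
- The same two corners give 0.802 and 0.655 for s = 0.60, and 0.915 and 0.835 for s = 0.80.
- b = 0.9, p = 0.3: v = 0.93, giving 0.70 / 0.979 = 0.715, close to the true 0.70.
- No biopsy and no PET-CT: v = 0, so sensitivity is 1.00 by construction.

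**3. Second model, with imperfect imaging and specificity included**

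Assumed: CA 19-9 sensitivity/specificity 0.70/0.80, CT growth 0.90/0.90, PET-CT 0.85/0.90, tests conditionally independent, decisive biopsy in a given share of those with CT growth. Results at recurrence prevalence 0.7 with PET-CT done in 30%, as apparent CA 19-9 sensitivity/specificity:

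| Biopsy share | Outcomes {12} rule | 2-of-3 rule | CA 19-9 removed (biopsy, otherwise CT growth) |
|---|---|---|---|
| 0 | 0.901/0.796 | 0.904/0.819 | 0.677/0.697 |
| 0.3 | 0.830/0.774 | 0.835/0.798 | 0.684/0.700 |
| 0.6 | 0.769/0.748 | 0.775/0.774 | 0.691/0.702 |
| 0.9 | 0.716/0.717 | 0.723/0.745 | 0.698/0.705 |

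Across all scenarios run (prevalence 0.4 or 0.7; PET-CT share 0, 0.3 or 1; biopsy share 0 to 0.9), apparent sensitivity under either protocol rule was 0.70 to 1.00. It was always above both the assumed true 0.70 and the CA 19-9-free reference. Specificity was 0.71 to 0.84, always above the CA 19-9-free reference (0.70 to 0.77) but on either side of the assumed true 0.80. It can fall below because recurrences missed by CT are counted as CA 19-9 false positives.

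**The case against.** Five points weigh on the other side.

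- **The rule is not mechanical.** The wording on clinical confirmation is permissive, the consensus criteria are given as examples, MRI is allowed, and the multidisciplinary meeting acts as the endpoint panel. Visits recur every three months, and disease-free survival is dated to the first radiological signs, so a lesion seen with normal CA 19-9 can be confirmed later and still count as a miss at the earlier visit. A reader might infer that a marker-negative lesion without biopsy or PET-CT can never be a false negative. The article does not support anything so absolute. This objection stands and reduces the size of the bias, not its direction.
- **Specificity.** A reader might infer that CA 19-9 accuracy as a whole will be overstated. Only sensitivity is firmly inflated. Specificity is raised relative to the same reference without CA 19-9, but its position against the truth is uncertain.
- **Size.** Every input is assumed. Strongly advised biopsy could mean a high biopsy share, and additional imaging is aimed at inconclusive cases, which may more often be marker-negative. Either would shrink the effect. The accuracy analysis does not state its cut-off, and bilirubin-adjusted values are planned, so the overlap may be partial. All of this stands.
- **Standing of the outcome.** It is one of many secondary outcomes, with no sample size attached. True, and the primary endpoint is not touched.
- **Detail left to an analysis plan.** This does not carry. The article itself defines recurrence and names its detection as the accuracy target, so the circularity is in what is written.

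**Conclusion.** The point holds in a limited form. As written, CA 19-9 sensitivity is calculated against a recurrence definition that uses CA 19-9 for cases without biopsy, and this biases it upward. The amount is unknown. Under the assumed shares in the simple model, a true 70% would read as about 75% to 86%, a true 60% as 66% to 80%, and a true 80% as 84% to 92%. With nearly universal biopsy the distortion is negligible. The direction for specificity against its true value is not established.

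CT accuracy has the same structural limitation, because CT growth is part of the clinical definition and CT suspicion starts the work-up. Its size has not been estimated here. Overall survival is unaffected, so this should be corrected but does not threaten the trial's main conclusion.

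**What to change.** For the CA 19-9 accuracy analysis only:

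1. Derive a recurrence variable that does not use CA 19-9: pathology where available, otherwise CT growth on consecutive scans and/or activity on PET-CT or MRI.
2. Report accuracy against that variable, together with a pathology-only analysis.
3. Show the figures under the protocol definition only as a sensitivity analysis, labelled as subject to incorporation bias, with the biopsy and PET-CT shares beside them.
4. State that CT accuracy shares the limitation.
5. Reconcile the clinical-confirmation definitions in Outcomes {12} and Abbreviations, and align the accuracy measures listed in Outcomes {12} and Statistical methods {20a}.

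The cost is analysis wording and one derived variable. It needs no new tests, provided that pathology, CT growth and other imaging results are recorded separately; the case record form is not shown, so this is an assumption. Some cases will become indeterminate and precision will fall slightly. An imaging reference also misclassifies: in the second model at a 60% biopsy share (prevalence 0.7, PET-CT in 30%), sensitivity moves from 0.769 to 0.691, nearer the assumed 0.70, while specificity moves from 0.748 to 0.702, further from the assumed 0.80. That trade-off should be stated.

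Two larger remedies are not proposed. A reference settled by a panel unaware of CA 19-9 would need masked re-adjudication, with 219 patients already enrolled at submission. Judging CT by subsequent surveillance rounds conflicts with trial follow-up ending at recurrence diagnosis.
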